**Methods:**

This controlled before-after study will accrue adult patients with acute chest pain, but without ST-segment elevation myocardial infarction on electrocardiogram for two years and is expected to include approximately 10,000 patients. Outcomes measures include hospitalization rate, objective cardiac testing rates (stress testing and angiography), length of stay, and rates of recurrent cardiac care for participants.

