### Study Timeline

Pre- and post-HEART Pathway ADP implementation cohorts will each accrue patients with acute chest pain for 1 year, with a 3-month wash-in period (Figure 1). Data will be collected electronically from all patients using health system electronic medical records (EMRs), and claims data from insurers will be used on a subset of patients insured by Blue Cross Blue Shield (BCBS) of North Carolina (the largest insurer in the state), MedCost, or North Carolina Medicaid.

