### Outcome Measures

Pre- and post-HEART Pathway cohorts will be compared for safety and health care utilization outcomes. The primary outcome will be hospitalization rate at 30 days for patients presenting with acute chest pain. Secondary outcomes will include index hospitalization rate, index and 30-day objective cardiac testing, hospital length of stay (LOS), recurrent ED visits, and nonindex admissions for chest pain. Outcomes will be assessed during the index visit and for 30 days thereafter.

Hospitalization will be defined as an inpatient admission or observation stay. Objective cardiac testing will be defined by any stress testing modality, coronary computed tomography angiography, or invasive coronary angiography. The modalities routinely available at Wake Forest Baptist Health include exercise ECG, exercise stress echocardiogram, dobutamine stress echocardiogram, coronary computed tomography angiography, stress nuclear imaging, stress cardiac magnetic resonance imaging, or invasive coronary angiography. LOS will be the time from ED arrival to hospital discharge for all patients, whether admitted or not. A recurrent visit to the ED will be defined as any patient revisiting the ED with chest pain or other symptoms suggestive of ACS within the 30-day follow-up period.

Safety outcomes will include death and acute MI within 30 days. Missed adverse events will be defined as death or MI occurring in patients discharged from the ED without objective cardiac testing. The definition of MI will be based on the Third Universal Definition of MI, which includes a rising or falling pattern of troponin with a cutoff representing the 99th percentile reference value with a coefficient of variation <10% [20].

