### Statistical Analyses

Logistic regression models, which include potential patient-level confounders such as age, sex, race, ethnicity, insurance status, and ACS risk factors in addition to the intervention indicator, will be used to assess the effect of the HEART Pathway intervention on hospitalizations (and other dichotomous outcomes such as objective cardiac testing and recurrent ED visits). As secular trends represent a threat to internal validity (observed differences between groups could be from time trends rather than the intervention), we will include the time since the start of the study in the models, as well as the time by intervention interaction. This will allow us to assess the effect of the HEART Pathway implementation on the proportion of patients hospitalized, as well as its effect on the time trend after implementation.

Continuous outcomes will be analyzed using multiple linear regression models including potential confounders, time, the intervention indicator (pre- or post-HEART Pathway implementation), and the time by intervention interaction as described above. LOS tends to be skewed, so we will use some transformation (log, rank, etc) in the analyses if necessary. Residuals will be examined to ensure the model assumptions (linearity, homoscedasticity, and normality) are met. Not all patients will have electronic follow-up data. The default assumption will be that patients without follow-up data from the EMR, insurers, or Social Security Death Masterfile did not suffer adverse events. Sensitivity analyses will be used to assess the impact of missing data on our results. The analyses will be repeated assuming all patients with missing follow-up data had follow-up events (hospitalization, cardiac testing, etc). Multiple imputation will be used to conduct sensitivity analyses that generate complete datasets under a variety of assumptions regarding the rates of outcomes in the two periods. All analyses will be performed using SAS 9.4 (Cary, NC). *P*<0.05 will be considered significant.

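### With time counted from study start, the intervention coefficient is a contrast on the first pre-period day, and the stated 90% power does not apply to it

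*Protocol article*

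**What the plan says.** All references are to the protocol article.

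- **Outcome Measures** names one primary outcome: "The primary outcome will be hospitalization rate at 30 days".
- **Statistical Analyses** specifies logistic regression with patient-level confounders and the intervention indicator. To guard against secular trends it adds: "we will include the time since the start of the study in the models, as well as the time by intervention interaction".
- The same section says what the model is for: "This will allow us to assess the effect of the HEART Pathway implementation on the proportion of patients hospitalized", and then "as well as its effect on the time trend after implementation". It gives no time point at which the first effect is read and does not rank the two. The only criterion is a P value below 0.05.
- **Study Timeline**: the two cohorts "each accrue patients with acute chest pain for 1 year, with a 3-month wash-in period".
- **Sample Size** expects 5000 patients per period, 4000 of them with follow-up, and a pre-period hospitalization rate of 53%. It claims 90% power at the two-sided 5% level for reductions below 5%, read here as percentage points.

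**The concern.** When a model contains an interaction with time, the main effect of the intervention is the contrast at the point where time equals zero. The article sets that point at study start, a year or more before any post-period patient is seen. The coefficient that a reader would take as the effect of implementation is therefore an extrapolation to a date when the pathway did not exist.

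Two things are at stake. The estimate can mislead about direction when the benefit grows, which is plausible here: the HEART Pathway Implementation section describes weekly tracking of use and corrective education of non-compliant providers. The extrapolation also makes the coefficient very imprecise, so the power claimed for the primary outcome belongs to a different test. The design has no concurrent comparison series, so this regression is the main protection against secular change.

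**Working it through.** **Inputs.** 53% pre-period rate, 4000 or 5000 patients per group, two-sided 5%, 90% power (Sample Size); 1 year per cohort and a 3-month wash-in (Study Timeline). Assumed: wash-in between the cohorts, uniform accrual, no covariates or clustering, variance evaluated at p = 0.53.

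**1. The stated power, reproduced.** For 53% against 48%:

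n = [1.96·√(2·0.505·0.495) + 1.2816·√(0.53·0.47 + 0.48·0.52)]² / 0.05² ≈ 2100 per group.

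With 4000 per group the power for this difference is 99.4%, and the difference detectable with 90% power is 3.6 points (3.2 with 5000). The claim is correct for an unadjusted comparison of two proportions.

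**2. What the coefficient means.** The model is logit(p) = b0 + b1·X + b2·t + b3·X·t. Post minus pre at time t is b1 + b3·t, so b1 is the contrast at t = 0, the first day of the pre period. The contrast at the start of the post period is b1 + b3·15 (t in months).

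**3. Precision.** A line fitted to uniform accrual over one year, read d years from the middle of that year, has its variance multiplied by 1 + 12d². The factor for the contrast is the average of the two lines. The crude SE at 4000 per group is √(2/(4000·0.53·0.47)) = 0.0448.

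- Study start: pre d = 0.5 gives 4; post d = 1.75 gives 37.75; average 20.9. SE = 0.0448·√20.9 = 0.205, or 4.57 times crude.
- Month 15: pre d = 0.75 gives 7.75; post d = 0.5 gives 4; average 5.9. SE = 0.109.
- Study start with no gap: pre 4, post d = 1.5 gives 28; average 16. SE = 0.179.

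**4. Power for a constant fall from 53% to 48%.** The log odds ratio is ln(0.48/0.52) − ln(0.53/0.47) = −0.200. Power is Φ(0.200/SE − 1.96) plus a negligible opposite tail.

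| Contrast | Power, 4000 per group | Power, 5000 per group | Fall from 53% detectable with 90% power, 4000 per group |
|---|---|---|---|
| Unadjusted | 99.4% | 99.9% | to 49.4% |
| Study start, 3-month gap | 16.5% | 19.4% | to 36.7% |
| Study start, no gap | 20.1% | 23.9% | to 38.7% |
| Month 15 | 45.4% | 54.0% | to 44.2% |

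**5. Sign.** On the risk scale with a flat pre trend, an immediate 5-point drop followed by a further 5 points per year gives −5 + 5·1.25 = +1.25 points at study start. On the log-odds scale, with 53% falling to 48% at month 15:

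- 44% by month 27 gives b1 = +0.001 (odds ratio 1.00);
- 40% by month 27 gives b1 = +0.207 (odds ratio 1.23), the wrong direction for a real and growing benefit.

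**6. Level and slope together.** If a success on either test were allowed, the false-positive rate with no effect would be 7.4% with the origin at study start (correlation of the two estimates −0.85) and 9.7% with the origin at month 15 (correlation 0.18). Two independent tests would give 1 − 0.95² = 9.75%.

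**The case against.** The strongest reply is that the article lists model terms and never says that the raw coefficient will be reported. The fitted model does not depend on the time origin, so a contrast at the start of the post period, or averaged over it, can be taken from the same fit, and an unseen analysis plan may do so. This stands in part: the model is not invalid. But the article goes beyond leaving the matter open. It fixes the origin at study start, ties the resulting model to the effect on the proportion hospitalized, and names no other contrast. The power mismatch also remains under any contrast calculated above.

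The sponsor also expects effects larger than 5 points. The abstract cites a 21% fall in hospitalizations in pilot data. If that means percentage points and the fall is constant, it exceeds the 16.3 points (53% to 36.7%) that the study-start coefficient can detect with 90% power. That does not rescue the claim made for reductions below 5%, nor the interpretation when the effect changes over time.

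Three further readings are tempting and not supported:

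- **Two chances of success.** A reader might infer that the trial wins on either level or slope. No such rule is stated, and hypothesis and power concern the hospitalization rate. The rates of 7.4% to 9.7% are only what the unranked wording would allow.
- **Seasonal bias.** Free slopes over single years do pick up part of an annual cycle: at the worst phase, 1.7 points per point of amplitude at month 15 and 3.5 at study start. But the documents give no amplitude, and a purely annual cycle cancels in a crude comparison of two full years. Season terms are a modelling choice.
- **Controlled.** The abstract says "This controlled before-after study will accrue adult patients with acute chest pain", while Study Design describes a pre-post interrupted time series without a control series. This is a separate wording error and does not show a fault in the model.

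**Conclusion.** The point holds. As coded, the intervention coefficient estimates a contrast 15 months before the post period (12 if there is no gap; Figure 1 is not shown, so the position of the wash-in is an assumption). It is not the effect at or after implementation, and it can be null or wrong-signed for a pathway whose benefit grows. Its SE is 4.57 times the crude SE, and its power for 53% against 48% is about 17% at 4000 per group and 19% at 5000. With no gap it is 20% and 24%, which does not change the conclusion. The 90% power statement is arithmetically right for an unadjusted test, but not for the planned model.

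The meaning of the coefficient is algebra and needs no assumption. The power figures rest on uniform accrual and no covariates or clustering; the sign examples also assume a flat pre trend. A reader might go further and infer that the data cannot answer the question. They can, once the right contrast is named.

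**What to change.** 1. In Statistical Analyses, code time and the interaction as time since the end of wash-in. Alternatively, keep the coding and pre-specify a post-period contrast from the same fit. Report it as a standardised risk difference.
2. Name that one contrast as the primary effect on 30-day hospitalization, and make the slope change secondary.
3. Restate Sample Size for that contrast. For a constant 5-point fall, the level change at the start of the post period has about 45% power at 4000 per group and 54% at 5000. A contrast at mid-post-period (month 21) reaches further beyond the pre-period data: variance factor [(1 + 12·1.25²) + 1]/2 = 10.4, SE 0.144 at 4000, power 28% (34% at 5000).
4. Separately, delete the word controlled from the abstract.
5. Optionally, add annual season terms as a sensitivity analysis. A sine and cosine pair lowers the month-15 power to 35% (42% at 5000).

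No new data are needed and the fitted model does not change. The cost is a less favourable power statement, which has to be accepted with the new wording.

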### Data Collection

The effectiveness of the HEART Pathway will be assessed using electronic outcome surveillance. EMR data will be collected on all patients with chest pain. Insurance claims data will be collected on patients with Medicaid, MedCost, and BCBS of North Carolina. Data will include patient demographics, past medical history, cardiovascular risk factors, ECG results, troponin results, HEART score and HEART Pathway assessments, ED and discharge diagnoses, disposition, index visit length of stay, objective cardiac testing (stress testing or angiography) at the index visit or within 30 days, recurrent ED visits, readmissions, and myocardial infarction (MI) or death within the follow-up period. Data extraction from the EMR data warehouse (Clarity) will be automated and programmed to pull prespecified data points into our database on patients meeting eligibility criteria on a weekly or monthly basis (Figure 3). Electronic surveillance leverages our informatics strengths and data sharing relationships with insurers, to provide efficient and accurate outcome data. Data accuracy is enhanced by avoiding recall bias inherent in other follow-up methods such as telephone calls. Electronic surveillance also improves feasibility by allowing programmable follow-up on a large number of patients at a low cost. Inclusion of Medicaid patient claims should ensure that our data surveillance includes economically disadvantaged patients and is generalizable to the patient populations of other hospitals. Any discrepancies between sources of data will be adjudicated by study investigators blinded to patient pre- or post-intervention cohort participation. Based on prior studies, we expect 80% of patients to have follow-up data from the EMR or insurer claims. The Social Security Death Master File will be used to search for participants without follow-up data.

The preintervention cohort will be identified using the same inclusion criteria (aged ≥ 21 years with a complaint of chest pain and a troponin ordered without STEMI on ECG) for 1 year prior to integration of the HEART Pathway into cardiovascular care delivery at Wake Forest Baptist Health. The same data elements described above will be abstracted from the EMR and claims databases from BCBS, MedCost, and Medicaid.

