### Sample Size

A sample size of approximately 10,000 patients, (5000) pre- and (5000) post-intervention, is anticipated. Based on prior studies it is expected that 80% (4000 patients/group) will have follow-up data from the EMR or insurer claims. With this sample size we will be able to estimate safety event rates for each study period to ±0.33% with 95% confidence (assuming an event rate of 1%). Based on our prior studies, we expect a hospitalization rate of 53% and an objective cardiac testing rate of 83% among hospitalized patients during the preintervention period [16,21]. This study will be adequately powered to detect reductions in hospitalization and objective cardiac testing rates of <5%, with 90% power at the 5% two-sided level of significance. We anticipate larger effects [16,17,22].

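### Treating patients without follow-up data as free of adverse events biases the 30-day death and MI rates low, by an amount that depends on how many of their events go uncaptured

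*Protocol article*

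**What the plan says.** Statistical Analyses in the protocol article states the rule: "The default assumption will be that patients without follow-up data from the EMR, insurers, or Social Security Death Masterfile did not suffer adverse events". The alternatives are called sensitivity analyses, so this is the main analysis. One of them is the opposite extreme: "The analyses will be repeated assuming all patients with missing follow-up data had follow-up events (hospitalization, cardiac testing, etc", and so on. The other is multiple imputation, with the assumed outcome rates varied over the two periods.

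Sample Size gives the scale: "A sample size of approximately 10,000 patients, (5000) pre- and (5000) post-intervention, is anticipated", and "it is expected that 80% (4000 patients/group) will have follow-up data from the EMR or insurer claims". It then quotes a per-period precision of ±0.33% for safety event rates, assuming a 1% rate.

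On deaths, Data Collection says: "The Social Security Death Master File will be used to search for participants without follow-up data". It describes no search for the other patients.

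Outcome Measures says: "Safety outcomes will include death and acute MI within 30 days". It defines missed adverse events as death or MI in patients sent home from the ED without objective cardiac testing.

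**The concern.** The study hypothesizes less hospitalization and testing with no increase in adverse cardiac events. Its default gives the favourable outcome to every patient whose outcome is unknown. This acts in two ways.

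- Any event in the missing group that no source captures is counted as a non-event, so the rate falls. Unknown outcomes also enter the denominator as if observed, so the interval shrinks.
- The death file, as described, is not used for patients who have some follow-up data. If such a patient has an early contact and later dies outside the system within 30 days, the death may not be found.

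Missed adverse events are the most exposed. They arise mainly after ED discharge, so index-visit data help little, and a death file cannot show a nonfatal MI treated at another hospital.

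**Working it through.** **Inputs.** From Sample Size: 5000 patients per period, 80% (4000) with follow-up, so 1000 without; event rate 1%; stated precision ±0.33%. From Statistical Analyses: missing patients are set to no event. The document does not give the event rate among missing patients or the share of their events that is captured, so both are varied below as assumptions.

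**The plan's own figure.** Half-width = 1.96 × √(p(1 − p)/n). With p = 0.01 and n = 4000 this is 0.308%. The exact (Clopper-Pearson) interval averages 0.322% per side. Neither rounds to 0.33%, which would need n of about 3492. The stated figure is slightly conservative, and nothing below depends on it.

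**The default rule at the planned rate.** Followed patients: 0.01 × 4000 = 40 events.

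- Followed patients only: 40/4000 = 1.00%, half-width 0.308%, interval 0.692% to 1.308%.
- Default: 40/5000 = 0.80%, half-width 1.96 × √(0.008 × 0.992/5000) = 0.247%, interval 0.553% to 1.047%.

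The default interval is about 20% narrower (0.247/0.308 = 0.80). Part of this comes from the larger denominator alone (0.276% at 1% and n = 5000), the rest from the lower estimate.

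**Varying the event rate r among the missing, none captured.** True rate = (40 + 1000r)/5000; the default stays at 0.80%.

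| r | True rate | Default relative to truth |
|---|---|---|
| 0% | 0.80% | no bias |
| 0.5% | 0.90% | 11% too low |
| 1% | 1.00% | 20% too low |
| 2% | 1.20% | 33% too low |
| 3% | 1.40% | 43% too low |

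At r = 2% and 3% the true rate lies above the default interval's upper limit of 1.047%.

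**Varying the share c of the missing group's events that is captured** (index-visit data or death file), with r = 1% and a true rate of 1%. Expected default rate = 0.8 × 1% + 0.2 × 1% × c. Coverage is the exact binomial probability that the nominal 95% Wald interval with n = 5000 contains 1%.

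| c | Default rate | Half-width | Coverage |
|---|---|---|---|
| 0 | 0.80% | 0.247% | about 65% |
| 25% | 0.85% | 0.254% | about 78% |
| 50% | 0.90% | 0.262% | about 87% |
| 75% | 0.95% | 0.269% | about 93% |

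For comparison, the followed-only interval covers about 94%.

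**The opposite extreme.** All missing as events gives (40 + 1000)/5000 = 20.8%. The two fixed scenarios therefore bracket a 1% outcome only between 0.8% and 20.8%.

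**Deaths among patients with some follow-up data.** The document gives no figure from which to size this. It would add to the bias above.

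**The case against.** The strongest reply is that the plan already contains most of the remedy. Multiple imputation with outcome rates varied by period comes close to a tipping-point analysis, and Limitations concedes that electronic surveillance may raise loss to follow-up. That stands, and it lowers the severity. It does not change which analysis is the default.

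The 20% is also not a block of patients with nothing known. Index-visit diagnoses and troponins are in the EMR for everyone, and deaths found in the file count. Patients sent home may also have a rate below 1% after discharge. All of this stands, so 65% coverage is close to the worst case for missing patients with the same risk as the others.

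Planned precision is based on the 4000 followed patients and is not too narrow. The narrowness arises only when the default is applied. The primary outcome is 30-day hospitalization, whose index part is known for all.

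On the death file, the text does not say that other patients are excluded, and the article does not define follow-up data. The concern rests on the search as described.

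Two stronger readings are tempting:

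- A reader might infer that the missing patients are mostly those discharged from the ED, so that up to 0.20/0.47 = 43% of discharged patients have unknown outcomes. That requires every hospitalized patient (53%) to be followed. The document gives no missingness by disposition.
- A reader might infer a false safety difference between periods. That needs missingness, or the events missed, to differ by period. The document states no such difference and plans the same data elements for both. Similar missingness would leave a relative comparison less affected, but each period's rate would still be low.

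**Conclusion.** The point holds for the per-period 30-day safety rates, and most strongly for missed adverse events. The direction follows from the rule itself: every uncaptured event lowers the rate, and unknown outcomes are counted as observed zeros. The size is conditional. At the planned 1% rate and 20% missing, the estimate is 0.80% (±0.25%) instead of 1.00% (±0.31%) if the missing share that rate and none of their events is captured, and about 0.90% with about 87% coverage if half are. There is no bias only if no event goes uncaptured. The all-events analysis does not help, because 20.8% is no useful bound for a 1% outcome. The planned multiple imputation softens the problem, so this is a should-fix and does not undermine the primary outcome.

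**What to change.** For the 30-day safety outcomes:

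- Make the already planned multiple imputation the main analysis, conditioned on period, disposition, insurer and baseline risk. Retain index-visit events and known deaths as observed.
- Keep the no-event rule, labelled as the best case.
- Present the varied-rate imputations as a tipping-point analysis by period, in place of relying on the all-events scenario.
- Report missingness by period and disposition.
- Run the death-file match on all patients, about 10,000 instead of about 2,000 (20% of 10,000).

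Do not replace imputation with an analysis of patients whose follow-up is verified by EMR contact at or after day 30. A patient who dies earlier cannot meet that criterion, so early deaths would drop out, and patients who return for care would be over-represented.

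The cost is slightly wider safety intervals, reliance on imputation assumptions that the tipping-point analysis makes visible, and one larger batch match. No new patient contact is needed.
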